#### Inclusion and exclusion criteria

Our inclusion criteria are as follows: 1) DSM-5-TR diagnosis of ADHD (including Predominantly Inattentive, Predominantly Hyperactive/Impulsive, or Combined types) through prior medical or psychological evaluations at the time of admission to the program, 2) ability to complete questionnaires and use an app in English (Spanish and other languages will be developed at a later time and are not feasible for the initial RCT), 3) reported IQ of at least 80 in order to ensure that the participant has the cognitive skills needed to use the app, and 4) parent/guardian available to consent and provide feedback in English.

Children will be included regardless of treatment status during recruitment and throughout the study (with or without medication and ongoing psychotherapy). Parents will be asked several questions at each assessment related to treatment, including whether the child is taking medications (with medications and dosage recorded, if applicable), whether the child is receiving psychotherapy (and frequency during the study period), and whether the child is receiving any other services (e.g., school-based occupational, speech, or educational therapies). These factors will be recorded in the database to examine any potential differences in outcomes based on existing treatment services. We will not ask parents to change any treatment protocols at enrollment or postpone any outside treatment services once enrolled.

Failure to meet any of the inclusion criteria will result in exclusion. There are no additional exclusion criteria, as we aim to recruit a sample that is generally like the community's population of children with ADHD to enhance the generalizability of the DHI.

#### Assessments

Participants will have four assessments: Baseline (1 week before the start of the intervention period), Week 8 of the intervention period, Week 16 of the intervention period (post-treatment), and 8 weeks later (follow-up). Delayed treatment (DT) participants will have an additional assessment that follows the waitlist period (Pre- Intervention). This design will create a starting point for future studies of longer-term outcomes that are presently beyond the scope of the proposed study. Completing the study measures will require up to one hour for the child and parent at each assessment. For clinicians and educators, completing the questionnaires will require approximately 20 min at each time point. In addition, at each assessment time point, we will conduct semi-structured interviews (~ 30 min each) with participants focused on issues specific to different points of care and experiences with the DHI. Assessments will take place within a 7-day window at each designated timepoint. We will schedule them at a time convenient to participants and will offer remote/virtual platforms to increase adherence.

#### Study sample size

A priori sample size calculation was performed for a parallel group design with four repeated measures. A total sample size of 60 children was identified as sufficient for detecting medium group differences with a type I error rate set to 5% and power set to 81% in response to the intervention across the 4-time points (G*power V3.1.9.6). In our study, we will recruit 60 children (ages 8–12) with ADHD and randomly assign them to one of four groups: immediate intervention, immediate active control, delayed intervention, and delayed active control, with 15 children in each group. For an R33 pilot clinical trial, we aimed for power > 80% as this would allow us to detect trends in outcomes that would inform future research, including a fully-powered randomized clinical trial.

### Quantitative data collection

We will collect quantitative data using (1) well-validated research measures and (2) data gathered from the DHI itself. In this way, we can triangulate the phenomena we observe and create robust models for self-regulation, response to various contextual cues, and our approach's feasibility, acceptance, and potential impact. Standardized outcome measures (see Table 1) will be administered at each assessment timepoint. Quantitative data from outcome measures will be collected to examine both proximal and distal outcomes in a longitudinal repeated measures design. Measures will assess behavioral mechanisms (e.g., self-regulation and self-monitoring), clinical outcomes (e.g., ADHD symptoms), and process outcomes (e.g., patient or provider experience with treatment).

**Table 1 Tab1:** Standardized quantitative outcome measures

Outcome	Data Sources	Instrument	Description
Child Self- Regulation *(primary outcome)*	Child, Parent, Teacher, Researchers	The Behavior Assessment System for Children (BASC-3) – Self, Parent, and Teacher Reports	BASC-3—a validated and nationally normed self-report scale of self-regulation, emotional, and behavioral symptoms that has been shown to produce reliable scores and has national norms for various symptom subscales
Parent Self- Regulation *(primary outcome)*	Parent	BASC-3 Parenting Relationship Questionnaire (PRQ)	The BASC-3 PRQ includes items that address Parent Self-Regulation, Parenting Confidence, and Parenting Stress
Self-Efficacy *(secondary outcome)*	Child	BASC-3 Self-Report	Self-ratings on self-efficacy, a dimension reflecting competence, capability, and problem-solving. The BASC-3 has three scales that address this domain, which will be examined: Sense of Inadequacy, Self-esteem, and Self-Reliance
Parent–Child Relationship *(secondary outcome)*	Child & Parent	BASC-3 Parenting Relationship Questionnaire (PRQ) BASC-3 Self Report (Relations with Parent scale)	The BASC-3 PRQ is a measure of a parent’s perspective on the parent’s relationship with the child. Our primary focus will be on the Relational Frustration scale The BASC-3 Self-Report measure for children includes scores for a subscale that addresses the parent–child relationship (Relations with Parent). Those scores will be examined to assess the impact of DHI on the parent–child relationship
Engagement in Care* (primary outcome)*	Child & Parent	Patient Activation Measure (PAM) and Parent Patient Activation Measure (Parent PAM)	The 13-item version of the PAM is designed to assess patient knowledge, skill, and efficacy in self-management of their condition. There is also a patient-focused version and a Parent PAM. We will use both in this study to examine the impact on engagement in care for both the child and the parent
Perceptions of Shared-Decision Making and Treatment Collaborations *(primary outcome)*	Child & Parent	Working Alliance Inventory-Short Revised	The Working Alliance Inventory-Short Revised is a 12-item validated scale that evaluates the working relationship between a client and a clinician
	Provider/Educator	Working Alliance Inventory-Short Revised	The Working Alliance Inventory-Short Revised has a provider version of a 12-item validated scale that evaluates the working relationship between a client and a clinician

Additional quantitative data will be gathered from children through smartwatches and parents via the parent smartphone application. This will include usage data and data measuring treatment adherence (e.g., taking medications as prescribed, completing treatment goals and intervention modules) and brief symptom reports (behavioral and emotional). In addition, we will also collect children's sensor data related to physical activity (e.g., bouts of exercise, step counts), sleep, and heart rate.

#### Planned analysis

Multilevel model analyses will be used to adjust for the non-independence (i.e., autocorrelation or clustering) of repeated observations nested within the same individual mixed effects. Such analysis will examine how outcomes within each patient change over time and how individual trajectories of change differ across patients. For each outcome, a mixed-effect model will be estimated with SAS PROC MIXED to test outcome differences between treatment groups at each repeated assessment and differences in the outcome trajectories. Momentary data collected via the scheduled DHI (CoolTaCo) entries will be aggregated to the weekly level, and generalized linear mixed effect models with Poisson distribution for count data will be estimated using SAS PROC GLIMMIX. Tukey adjusted tests will be used for post-hoc comparisons to evaluate significant changes between two time points, treatment groups, or other paired comparisons when a significant interaction was revealed.

Preliminary analyses will be conducted to identify potential individual characteristics (e.g., gender) to be included as covariates. An important strength of multilevel models is the ability to account for unbalanced and/or missing data (which are common problems in ecological momentary data collection) by not placing restrictions on the number of observations obtained for each individual and allows trajectories across time to be estimated from an individual’s available data.

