### RCT design

We will recruit 60 children (ages 8–12) with ADHD who will be randomized to either immediate (*n* = 30) or delayed (*n* = 30) treatment (i.e., a waitlist control group). Among those randomized to immediate treatment, half will be assigned to DHI (an intervention delivered via a smartwatch for the child and smartphone application for the parent), and half will be assigned to an active control [treatment as usual (TAU)] group. Individuals in the TAU group will receive the smartwatch with no assigned activities or applications. The intervention period will last 16 weeks, and participants will complete study assessments before, during, and after the intervention period. Participants randomized to delayed treatment will wait for 16 weeks; they will complete an assessment before and after the waiting period. After this waiting period, they will be randomly assigned to either DHI or TAU. Thus, 30 participants will complete 16 weeks of DHI, and 30 will be followed for 16 weeks of TAU, with half of the total sample also completing a waitlist period.

We will loan smartwatches and phones as necessary for the study in both the DHI and the TAU groups. Participants will be taught basic cybersecurity and privacy best practices, including how to lock and encrypt phone data.

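### Weekly Poisson counts of app entries have no stated denominator, so for symptom, event and self-entered adherence counts a missed entry reads as a low value that the claimed missing-data safeguard does not reach

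*Protocol article*

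**What the plan says.** Under *Quantitative data collection*, the article lists data gathered through the watch and the parent phone app: "This will include usage data and data measuring treatment adherence", together with short symptom reports. Passive sensor data are listed separately: "we will also collect children's sensor data related to physical activity (e.g., bouts of exercise, step counts), sleep, and heart rate".

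*Planned analysis* describes how the app entries are handled: "Momentary data collected via the scheduled DHI (CoolTaCo) entries will be aggregated to the weekly level". For the model itself, the section then specifies that "generalized linear mixed effect models with Poisson distribution for count data will be estimated using SAS PROC GLIMMIX". It names neither the number of scheduled or completed entries as a denominator nor any allowance for overdispersion.

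The next paragraph of that section names as a strength of multilevel models their "ability to account for unbalanced and/or missing data (which are common problems in ecological momentary data collection"), on the ground that each child may contribute a different number of observations.

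On the comparison arm, *RCT design* states: "Individuals in the TAU group will receive the smartwatch with no assigned activities or applications". The same section adds: "We will loan smartwatches and phones as necessary for the study in both the DHI and the TAU groups".

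**The concern.** A mixed model fitted by likelihood copes with a missing outcome by leaving that row out and using the child's other rows. This works only if missingness shows up as an absent value. Once several scheduled entries in a week are collapsed into one count, a partly completed week still has a value, only a smaller one. The model cannot distinguish fewer symptoms from fewer reports.

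The article itself expects missing momentary data to be common, and *Potential problems and strategies* anticipates data loss from uncharged devices. If completion wanes over 16 weeks, symptom counts fall with it and the intervention appears to help. Adherence known only through an entry falls in the same way, although not reporting an action is different from not doing it.

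The second issue is precision. A Poisson model sets the variance equal to the mean, given the child effects. Random effects absorb differences between children. An intercept does not absorb week-to-week variation within a child, and any such excess makes the standard error of a time trend too small.

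Finally, scheduled CoolTaCo entries can arise only under DHI, so a trend in them is a within-arm description and not a randomised effect.

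**Working it through.** The article gives no figure for this point to reproduce. Its one design figure, 81% power, concerns the repeated assessments and does not bear on this model.

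**Inputs from the article:** 30 children complete DHI for 16 weeks (*RCT design*); weekly aggregation and Poisson mixed model (*Planned analysis*); type I error 5% (*Study sample size*).

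**Assumed inputs:** 14 scheduled entries a week; constant probability 0.3 of a symptom report per completed entry; completion falling linearly from 90%; for the dispersion check, a weekly mean of 4. Between-child SD is 0.4, on the logit scale for the first simulation and on the log scale for the second. No true time trend in either.

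**1. Missed entries.** Expected weekly count = scheduled entries × completion × rate per entry. With completion falling from 90% to 70%:

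- week 1: 14 × 0.9 × 0.3 = 3.78
- week 16: 14 × 0.7 × 0.3 = 2.94
- ratio: 2.94 / 3.78 = 0.778

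The scheduled number and the rate cancel, so the false ratio is final completion divided by initial completion. A fall to 60% would give 60/90 = 0.667, a spurious 33% decline.

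Simulation used a log-linear Poisson trend with child-clustered robust standard errors, 300 runs per row:

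| Completion | Ratio by arithmetic | No offset: rate ratio | No offset: rejects | Offset: rate ratio | Offset: rejects |
|---|---|---|---|---|---|
| 90% to 70% | 0.778 | 0.785 | 94% | 1.006 | 5.0% |
| 90% to 50% | 0.556 | 0.561 | 100% | 1.000 | 8.0% |
| 90% to 30% | 0.333 | 0.359 | 100% | 0.995 | 7.0% |

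The offset is log(completed entries); weeks with none are dropped. Monte Carlo error of a true 5% rate over 300 runs is √(0.05 × 0.95 / 300) = 1.3 percentage points, so the offset removes the bias and leaves the test at or slightly above its nominal level.

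**2. Overdispersion.** If the residual variance is φ times the mean, the model standard error is too small by √φ and the true rejection rate is 2(1 − Φ(1.96/√φ)):

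- φ = 2: factor 1.41, rejection 16.6%
- φ = 3: factor 1.73, rejection 25.8%

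Random-intercept Poisson models fitted to simulated data with gamma week-to-week noise (150 runs each; variance/mean stated at a mean of 4) gave:

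| Variance/mean | True SD / model SE | Rejection at nominal 5% |
|---|---|---|
| 1 | 0.93 | 4.0% |
| 2 | 1.46 | 20.0% |
| 3 | 1.98 | 32.7% |

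The simulated values exceed the formula because gamma noise makes variance/mean grow with the child's own mean (1 + α × mean, with α = 0.25 or 0.5), and high-count children carry more weight. The mean weighted in this way is 4 × exp(1.5 × 0.4²) = 5.08. Then φ = 1 + 0.25 × 5.08 = 2.27 and 1 + 0.5 × 5.08 = 3.54, the factors are 1.51 and 1.88, and rejection is 19% and 30%. These agree with the simulation within its error (3.3 and 3.8 percentage points).

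A marginal Poisson model with cluster-robust standard errors rejected 4.0%, 8.4% and 4.8% at variance/mean 1, 2 and 3 (500 runs each). This is much closer to nominal, though 8.4% exceeds simulation error (1.0 point at a true 5%).

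**The case against.** The strongest reply is that a journal article need not give offsets, scale parameters or minimum valid days, which belong in an SAP that is not shown. Naming a Poisson mixed model for counts is an ordinary choice of family and excludes none of these refinements. That is fair, and the missing dispersion term alone would not be a finding. What remains is that the article makes a positive claim, that the model accounts for missing momentary data, and for within-week misses in the affected counts this claim fails under the model as described.

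Several stronger readings do not stand:

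- **That the plan says it sums entries.** The text says only that they are aggregated. Summation is inferred from the use of a count distribution, and symptom reports might be ratings analysed otherwise.
- **That all app counts are biased.** For usage and module completion, a missed entry is a genuine low value and waning use is the outcome itself.
- **That overdispersion is present.** The article gives no evidence on it, the child effects absorb part of it, and counts near the ceiling of scheduled entries could be underdispersed, which errs the other way.
- **That a DHI versus TAU Poisson test is planned.** The Tukey sentence mentions treatment groups only generically and is not tied to this model.
- **That all device data are confined to DHI.** Watches and phones are loaned in both arms, so sensor data may exist under TAU.

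**Conclusion.** The point holds for symptom and event counts, and for adherence captured only by self-entry. For these, the missing-data safeguard covers weeks without data but not entries missed within an observed week. The false trend equals the ratio of final to initial completion: about 0.78 for a fall from 90% to 70%, and 0.56 for a fall to 50%. Completion rates are assumed, since the article gives none. The calculation also takes missed entries to be like completed ones.

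The precision problem is conditional. If residual variance/mean is 2 to 3, standard errors are about 1.5 to 2 times too small and a 5% trend test rejects about 20% to 33% of the time. If no overdispersion remains, there is no such problem (4.0% in simulation).

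A reader might infer that the trial's main results are at risk. They are not: every outcome labelled primary or secondary in Table 1 is a standardised scale completed at the assessments, and none depends on this model. The point concerns additional app outcomes in a trial that the article describes as a pilot. It is worth correcting because the error can look like benefit and the correction is cheap.

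**What to change.** In the analysis plan, and in one or two sentences of any later report:

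- Define each weekly count and say whether a missed entry is a true zero (usage, module completion) or an unobserved value (symptoms, events, self-entered adherence).
- Model entry completion as binomial: completed out of scheduled.
- Model symptom and event counts with log(completed entries) as offset, and treat weeks with no entries as missing. For adherence known only by self-entry, use completed entries as the denominator likewise.
- Allow for dispersion by a negative binomial model, an estimated scale or robust standard errors.
- Limit the missing-data statement to weeks without data.
- Label app-entry analyses as within-DHI and descriptive. Any between-arm device comparison should use only sensor data collected in both arms.

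The cost is a few lines of GLIMMIX code and slightly wider intervals. The offset corrects for how many entries were completed. It does not correct for children skipping entries because of how they feel that day, so completion should be reported beside each symptom trend. If the unseen SAP already contains these steps, correcting the missing-data sentence is enough.

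### No deciding baseline-adjusted DHI–TAU contrast is named, and Tukey group comparisons wait for a significant interaction; naming one direct contrast would give more power from the same data

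*Protocol article*

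**What the plan says.** The Planned analysis section fits a mixed model for each outcome in order to "test outcome differences between treatment groups at each repeated assessment and differences in the outcome trajectories". That sentence has no gate and no multiplicity adjustment. A separate sentence says that "Tukey adjusted tests will be used for post-hoc comparisons to evaluate significant changes between two time points, treatment groups, or other paired comparisons", and limits this to cases "when a significant interaction was revealed". The set of pairs that Tukey covers is not defined.

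Covariates are to be picked from individual characteristics after preliminary analyses, with gender as the example. The baseline value of the outcome is not mentioned.

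The Assessments section says "Participants will have four assessments: Baseline (1 week before the start of the intervention period), Week 8 of the intervention period", followed by Week 16 and a follow-up eight weeks later. The Study sample size section says "A priori sample size calculation was performed for a parallel group design with four repeated measures", and that 60 children are "sufficient for detecting medium group differences" at a 5% type I error rate with 81% power. Together these suggest that baseline is one of the four response visits, but the model sentence does not say so.

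**The concern.** A two-arm comparison in 60 children has little power to spare, and three features of the text can use it up:

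- A group-by-time interaction over four visits has 3 degrees of freedom. It spreads power over every way in which two profiles can differ.
- Requiring that interaction to be significant before comparing the groups means that two tests must both succeed.
- A visit-wise comparison without the baseline score ignores information that the trial already collects.

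The plan also offers several tests per outcome and does not say which one decides. If they disagree, the reader cannot tell whether the outcome was met. Testing the groups at every assessment appears to include baseline, where any difference between randomised arms is chance.

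**Working it through.** **Inputs from the protocol article.** N = 60, DHI 30 vs TAU 30, four assessments including baseline, alpha 5%, power 81%, and an effect described only as medium.

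**Assumptions (not in the document).** Medium means f = 0.25, or d = 0.5. SD is 1, with compound symmetry at correlation ρ = 0.5, 0.6 or 0.7, no dropout and two-sided tests.

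**The plan's own figure.** The 81% can be reached in at least two ways:

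- Two-group interaction with λ = f²·N·(m−1) = 0.0625 × 60 × 3 = 11.25 on (3, 174) df: 80.4%.
- Two-group between-subject test with λ = f²·N·m/(1+(m−1)ρ) = 15/(1 + 3 × 0.267) = 8.33 on (1, 58) df: 81%.

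The text does not say which test was powered. So 81% cannot be attached to a particular test in the Planned analysis section.

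**Power of the routes, sustained effect (0, 0.5, 0.5, 0.5).**

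1. *Interaction.* λ = (n/2)·Σ(δ_j − δ̄)²/(1−ρ). The mean effect is 0.375, so the sum of squares is 0.375² + 3 × 0.125² = 0.1875. At ρ = 0.5, λ = 15 × 0.1875/0.5 = 5.625 on (3, 174) df, giving 48%. The λ of 11.25 above would need 2.8125/(1−ρ) = 11.25, that is ρ = 0.75.
2. *Unadjusted Week 16 difference.* 0.5/√(2/30) = 1.94 on 58 df: 48%, whatever ρ is.
3. *Baseline-adjusted Week 16 contrast.* The residual variance is 1 − ρ². At ρ = 0.5, 0.5/√(2/30 × 0.75) = 2.24 on 57 df: 59%.
4. *Baseline-adjusted mean of the three post-baseline visits.* The residual variance is (1+2ρ)/3 − ρ². At ρ = 0.5 this is 0.417, and 0.5/√(2/30 × 0.417) = 3.00 on 57 df: 84%.
5. *Gated results.* These are simulated, because the gate and the pair test are correlated. For Tukey over the 2 × 4 = 8 cell means (28 pairs), the critical |t| is q(0.95; 8, 174)/√2 = 3.07. Without the gate that gives 13% at Week 16.

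| Test | ρ = 0.5 | 0.6 | 0.7 |
|---|---|---|---|
| 3-df interaction | 48% | 58% | 72% |
| Linear-slope interaction | 45% | 53% | 65% |
| Week 16, unadjusted, no gate | 48% | 48% | 48% |
| Gate, then unadjusted Week 16 | 27% | 30% | 36% |
| Gate, then 28-pair Tukey, Week 16 | about 10% | about 10% | about 10% |
| Week 16, baseline-adjusted | 59% | 66% | 76% |
| Post-baseline mean, baseline-adjusted | 84% | 88% | 93% |

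If the model used the four groups of 15 described under Study sample size, the interaction would have 9 df and 30%, 38% and 51% power.

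**Other effect patterns (same ρ values).**

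| Pattern at Week 8, Week 16, follow-up | Interaction | Slope | Week 16 adjusted | Mean adjusted |
|---|---|---|---|---|
| 0.25, 0.5, 0.5 | 44 / 54 / 68% | 57 / 66 / 79% | 59 / 66 / 76% | 69 / 74 / 81% |
| 0.25, 0.5, 0.25 | 33 / 41 / 53% | 23 / 28 / 35% | 59 / 66 / 76% | 50 / 55 / 63% |

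**The case against.** A reader might infer that the DHI–TAU effect can be reached only through the gate and Tukey, and that power is therefore about 10%. The documents do not support that. The sentence on testing groups at each assessment is ungated. The 10% also needs a 28-pair Tukey family that the text does not define; applied to two groups within one visit, Tukey carries no penalty.

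Nor does the text establish that baseline is analysed as an outcome visit. This is inferred from the count of four measures. Even if true, it need not cost power when the baseline means are constrained to be equal.

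It would also be too strong to say that a medium effect would usually be missed. The interaction alone has 58–72% at ρ of 0.6 to 0.7. Against a baseline-adjusted Week 16 contrast it loses only 11, 8 and 4 points at the three correlations, and nothing at ρ = 0.8 (89% for both).

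The trial has declared interests in trajectories and maintenance, so a trajectory test is not irrelevant. An omnibus test followed by Tukey is conventional, the trial is a pilot, and a condensed article may leave covariates and the exact contrast to an analysis plan.

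These points narrow the concern but do not remove it. The article does more than omit detail: it states a procedure, and that procedure makes the pairwise group comparisons conditional on an interaction. The kindest gated reading still gives only 27–36%. The ungated route, unadjusted, gives 48% where baseline adjustment gives 59–76%. The pilot label does not settle it either, because the article itself aims for power above 80%.

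**Conclusion.** The concern holds as a point of efficiency and clarity, not as an error that invalidates the analysis. The stated procedure names no deciding DHI–TAU contrast, does not name the baseline score as a covariate, and places Tukey group comparisons behind an interaction test.

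Under the sustained-effect assumptions, the loss against a baseline-adjusted Week 16 contrast is about 4 to 11 points for the interaction and 11 to 28 points for the unadjusted visit test. Against the adjusted post-baseline mean, the interaction loses about 21 to 36 points.

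The direction is firm over ρ of 0.5 to 0.7, but the size is not. It depends on the correlation, the effect pattern and the Tukey family, none of which the article gives. The averaged contrast is not always the best choice: if the effect fades after Week 16, the Week 16 contrast has more power.

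**What to change.** In the PROC MIXED model, either enter the baseline score as a covariate with the post-baseline visits as the response, or keep all four visits and constrain the baseline means to be equal. State which assessment is the baseline for delayed children, who have an additional one after the wait.

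For each primary outcome, prespecify one DHI-minus-TAU contrast: Week 16, or the average of the post-baseline visits if a sustained effect is the target. Fix that choice before data are seen. Test the contrast directly, without the interaction gate and without Tukey. Report visit-wise and trajectory results as supportive, and do not test baseline differences.

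The cost is analysis wording; no extra children, visits or measures are needed. The downsides are that the trajectory test becomes supportive and that an averaged contrast is less specific to Week 16, so the visit-wise estimates should be shown beside it.
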